## Abstract

**Introduction:**

The objective of this study is to evaluate whether intermittent hypoxia can enhance physical recovery following the induction of delayed onset muscle soreness (DOMS).

**Methods and analysis:**

A randomized controlled trial will be conducted with male participants aged 18–35 years who engage in at least two organized training sessions per week. After a DOMS induction protocol targeting the hamstrings, participants will be randomized to receive either intermittent hypoxia, hypoxia–hyperoxia, or placebo for five consecutive days. During this period, several outcome variables will be assessed, including: cognitive function—attention and executive functions (D2 Test and Trail Making Test A and B); stress (DASS-21 questionnaire); physical performance—VO_2_max, countermovement jump (CMJ, My Jump App), 30-m sprint speed (MySprint App), one-repetition maximum in half-squat (Vitruve linear encoder), isometric hamstring strength (ActivForce2 dynamometer), muscle soreness (VAS scale), heart rate variability, muscle oxygen saturation, hip flexion range of motion with extended knee (Goniometer Pro App); and blood inflammatory markers: HIF-1α, PGC-1α, Klotho protein and lactate. To analyze the effects of the intervention, a repeated-measures ANOVA will be performed to assess Group × Time interactions.

**Ethics and disseminations:**

The study was reviewed and approved by the Medical Ethics Committee of Hospital Clínico San Carlos, Madrid, Spain (internal code 25/446-E) prior to data collection. If effective, intermittent hypoxia and hypoxia-hyperoxia could be implemented as non-pharmacological recovery strategies for athletes and physically active populations, offering a novel alternative to current methods with inconsistent results. The findings may guide future research on hypoxic conditioning, inform clinical practices for rehabilitation and performance recovery, and potentially shape policy regarding safe, evidence-based applications of hypoxia in sports medicine.

**Clinical Trial Registration:**

https://www.anzctr.org.au/, registration code ACTRN12625001404415.

## Introduction

1

Delayed onset muscle soreness (DOMS) triggers increased neural activity driven by inflammatory mediators, negatively impacting performance (1–3). Although several approaches have been investigated to reduce DOMS, their effectiveness varies, yielding inconsistent results across different demographic groups and exercise regimens (4).

Intermittent hypoxia (IH) is an emerging strategy that alternates between exposure to hypoxic environments (low oxygen availability) and normoxic environments (normal oxygen availability, similar to altitudes below 1,800 meters) (5). Originally developed to mimic the benefits of high-altitude training, IH has demonstrated several physiological advantages, including improved mitochondrial function, reduced inflammation, enhanced oxygen transport, and increased capillary formation—all of which are critical for muscle recovery (6). Moreover, the activation of hypoxia-inducible factors (HIFs) in response to IH has been linked to favorable adaptations that promote recovery and enhance performance (7). Beyond muscle regeneration, IH also influences oxidative stress and inflammation, two key contributors to DOMS (8). Research suggests that controlled hypoxic exposure can strengthen the body's antioxidant defenses and reduce the production of proinflammatory cytokines (9). This implies that IH could potentially mitigate the pain, stiffness, and inflammation associated with DOMS, although no published studies have yet addressed this topic.

Another promising approach is hypoxia–hyperoxia (HH), which alternates between hypoxic (low oxygen availability) and hyperoxic (high oxygen availability) conditions (10). The rapid transition between hypoxia and hyperoxia is believed to stimulate angiogenesis, mitochondrial biogenesis, and metabolic efficiency, all of which facilitate adaptation and muscle recovery (11). The additional oxygen surge during the hyperoxic phase may also enhance tissue oxygenation, support the clearance of metabolic waste, and reduce muscle fatigue (12). A key element in this process is the activation of hypoxia-inducible factor 1-alpha (HIF-1α), the central regulator of cellular responses to low oxygen availability (13). HIF-1α promotes the expression of peroxisome proliferator-activated receptor gamma coactivator 1-alpha (PGC-1α), a critical regulator of mitochondrial biogenesis (6, 9). Moreover, DOMS is also associated with global fatigue and altered sensorimotor and perceptual states, which may transiently affect central processes such as attention (14). Emerging evidence indicates that hypoxic-based interventions, including intermittent HH, modulates neural, autonomic, and inflammatory pathways, and could simultaneously affect both physical recovery from DOMS and cognitive processes impaired during post-exercise fatigue (15). Accelerating recovery from DOMS may therefore contribute not only to restored sports performance but also to the recovery of attentional and cognitive functions, which are recognized as relevant components within the multifactorial determinants of athletic performance and injury risk (16).

The novelty of this research lies in exploring IH and HH exposure as comprehensive methods for muscle recovery, as they may influence not only muscle repair but also cognitive recovery and mental performance, which are often impaired by DOMS (17). Beyond localized muscle soreness, DOMS induces systemic and peripheral inflammatory responses and sustained nociceptive signaling that engage central somatosensory and motor processing networks, potentially influencing cognitive and psychomotor performance during recovery from intense exercise (18). The purpose of this study is to determine whether HH and IH can be effective techniques for DOMS recovery. Our hypothesis is that both HH and IH will accelerate recovery from DOMS. Additionally, given the alternating hyperoxic stimulus and the potentially amplified cellular signaling associated with hypoxia–hyperoxia protocols, we hypothesize that hypoxia–hyperoxia may induce greater improvements in recovery-related outcomes than intermittent hypoxia alone (17).

## Methods

2

### Study setting

2.1

This study is a prospective, longitudinal, randomized controlled trial conducted at Universidad Europea de Madrid, utilizing the university's physiology and sports performance laboratories. The trial will be carried out in accordance with the CONSORT guidelines (19).

The study will adhere to the ethical principles outlined in the Declaration of Helsinki. Prior to participation, all subjects will provide written informed consent, confirming that they understand the study procedures, potential risks, and their right to withdraw at any time. The study protocol was reviewed and approved by the Medical Ethics Committee of Hospital Clínico San Carlos, Madrid, Spain (internal code 25/446-E).

### Participants and eligibility criteria

2.2

Participants in this study will be men aged 18–35 years who engage in at least two organized training sessions per week. Recruitment will take place through university teams at Universidad Europea de Madrid (Spain), including sports clubs and training groups.

Participation will be entirely voluntary, and prior to enrollment, individuals will be required to sign informed consent forms after receiving a comprehensive explanation of the study objectives, procedures, and potential risks.

Only male participants will be included in order to reduce physiological variability associated with sex-specific hormonal fluctuations that may influence inflammatory responses, muscle damage markers, and autonomic regulation following eccentric exercise (20). In addition, hypoxic exposure can induce cardiovascular and ventilatory adaptations that may be modulated by hormonal status, potentially introducing additional variability in mixed-sex samples (7, 20).

Exclusion criteria will include: prior exposure to hypoxia training (to avoid pre-existing adaptations to hypoxia); a history of respiratory conditions contraindicating hypoxia exposure, such as asthma or chronic obstructive pulmonary disease; use of anti-inflammatory medication or other treatments that could interfere with recovery (e.g., cold water inmersion, massage therapy); the presence of musculoskeletal, neurological, or cardiovascular disorders that could impair recovery; and a diagnosis of schizophrenia—not due to the intervention itself, but because the use of a mask could potentially trigger an episode.

### Blinding and randomization

2.3

After recruitment, participants will complete the International Physical Activity Questionnaire (IPAQ). The sample will be matched by age and prior physical activity levels before randomization. Randomization will then be performed using a computer-generated random sequence created with Microsoft Excel, applying a 1:1:1 allocation ratio to assign participants to the intermittent hypoxia, hypoxia–hyperoxia, or placebo groups (19).

Participants will be allocated to coded groups (e.g., Group A, B, or C), without any indication of the intervention received. To ensure allocation concealment, the randomization sequence will be generated and managed by an investigator not involved in participant recruitment, data collection, or outcome assessment. Group assignments will be stored in a password-protected file and revealed only to the technician responsible for operating the hypoxic system, who will not participate in any assessments or data analysis (19).

To further reduce bias, the study will employ a triple-blind design: participants will not know their group allocation, evaluators will be unaware of the intervention administered to each subject, and data analysts will work exclusively with coded datasets without access to group identities.

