### Sample size

2.4

The primary outcome of this trial is hamstring isometric strength. The required sample size was determined *a priori* using G*Power 3.1 considering a repeated measures of variance (ANOVA) design. In the absence of prior data to inform the expected magnitude of change, a conventional medium effect size (*f* = 0.25), as defined by Cohen, was assumed. With a significance level of *α* = 0.05, a statistical power of 0.80 (*β* = 0.20), and six time points, the analysis indicated that 36 participants would be required to detect statistically significant differences between groups. To account for potential dropouts and non-compliance, an additional 20% contingency was applied, increasing the total sample size to 45 participants (15 per group).

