### Statistical analysis

2.7

All statistical analyses will be performed using IBM SPSS Statistics version 29 (IBM Corp., Armonk, NY, USA). The primary confirmatory analysis will focus on hamstring isometric strength. The normality of the variables will be assessed using the Shapiro–Wilk test. Descriptive analysis will be performed using the mean ± standard deviation for normally distributed data, or the median and interquartile range for data not following a normal distribution.

The principal analysis will evaluate the Group × Time interaction using repeated-measures ANOVA, as this term reflects the differential effect of the intervention over time between groups. When significant interaction or main effects are observed, Bonferroni-adjusted *post hoc* comparisons will be conducted. Effect size will be evaluated using partial eta squared (*η*^2^*p*).

Analyses will be conducted according to the intention-to-treat principle, including all randomized participants in the groups to which they were allocated. Missing data will be handled using multiple imputation procedures under the missing-at-random assumption prior to conducting the repeated-measures ANOVA.

Secondary outcomes will be analyzed using the same analytical approach. Where multiple comparisons across secondary endpoints are conducted, Bonferroni correction will be applied within each family of related outcomes.

Cognitive and psychological variables will be analyzed on an exploratory basis. Correlation analyses (Pearson or Spearman) and multiple linear regression models will be performed to explore potential associations and predictors of cognitive improvement or functional recovery. The level of statistical significance will be set at *p* < 0.05.

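### Participants are matched on age and activity before randomization, but neither the allocation sequence nor the primary model is tied to the matching; if arms are allocated within sets, the planned test may be conservative

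*Protocol article*

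**What the plan says.** Protocol article, section 2.3 (Blinding and randomization): after recruitment and completion of the IPAQ, "The sample will be matched by age and prior physical activity levels before randomization". The next step reads: "Randomization will then be performed using a computer-generated random sequence created with Microsoft Excel", "applying a 1:1:1 allocation ratio". The section does not say how sets are formed, how large they are, or whether the sequence runs inside them.

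Section 2.4 (Sample size): "The primary outcome of this trial is hamstring isometric strength". The calculation gives 36 participants, raised to 45 (15 per group) for dropout, and makes no reference to matching.

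Section 2.7 (Statistical analysis): "The principal analysis will evaluate the Group × Time interaction using repeated-measures ANOVA". The model named there has Group and Time. It has no matched-set factor and no covariate for age or physical activity.

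**The concern.** Matching before randomization restricts the design, and a restriction helps only if it is used twice: once when arms are assigned and again when the error term is formed. Here it is announced but appears in neither place.

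There are two possibilities:

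- **Arms are permuted within matched sets.** The trial is then a randomized block design analysed as if it were completely randomized. Group means differ by chance less than the ANOVA supposes, so the type I error falls below 5% and power may be lost.
- **The sequence takes no account of the sets.** The planned analysis then fits the design, but the matching sentence describes a step that balances nothing.

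Either way, section 2.3 and section 2.7 do not describe one coherent design. In a trial of 15 men per group, a lost gain in precision could matter.

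**Working it through.** **1. The plan's own figures.** 36 / (1 − 0.20) = 45, so the dropout inflation reproduces. The 36 cannot be checked, because section 2.4 gives neither the within-person correlation nor a sphericity correction. With correlation 0.5 and no correction, the interaction test needs 24. It needs about 36 only with, for example, a correlation near 0.25, or 0.4 with a correction factor of 0.75.

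**2. Inputs.** From the documents: 3 groups, 6 time points, α = 0.05, f = 0.25, 36 evaluable men. Assumed: within-person correlation 0.5, sets of three (12 triplets), and the share of within-person change in strength that the matching explains.

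**3. Degrees of freedom for the Group × Time error.**
- Planned model: (36 − 3) × (6 − 1) = 165.
- With set × time removed: 165 − (12 − 1) × (6 − 1) = 110, one third fewer.
- With age × time and IPAQ × time instead: 165 − 2 × (6 − 1) = 155.

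**4. Matching that explains strength level only.** Group × Time already excludes stable differences between men, so there is nothing to gain. The noncentrality is λ = f² × N × m / (1 − ρ) = 0.0625 × 36 × 6 / 0.5 = 27. Power is 0.960 on 10 and 165 df, and 0.954 on 10 and 110 df.

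**5. Matching that also explains change, with arms allocated within triplets.** Simulation, 3,000 runs per row, with matching explaining 30% of strength level in every row:

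| Share of change explained (assumed) | Type I error, without vs with set × time | Power, without vs with set × time |
|---|---|---|
| 0% | 0.054 vs 0.051 | 0.895 vs 0.885 |
| 10% | 0.024 vs 0.050 | 0.855 vs 0.904 |
| 20% | 0.009 vs 0.048 | 0.837 vs 0.945 |

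The Monte Carlo standard error near 5% is √(0.05 × 0.95 / 3000) = 0.004. The simulated effect differs from the one in step 4 (power in the 0% row is 0.895, not 0.960). The powers should therefore be compared within a row and not read as this trial's power.

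**6. Cross-check of the type I errors.** If a share s of change belongs to the sets, the interaction mean square is about (1 − s) times what the planned error term implies. The type I error is then about P(F on 10, 165 df > 1.888 / (1 − s)). For s = 0.10 the cut-off is 2.098, giving 0.027. For s = 0.20 it is 2.361, giving 0.012. Both are close to the simulated 0.024 and 0.009.

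**7. Allocation that ignores the sets.** Across the same scenarios the planned test had type I error between 0.041 and 0.059, so its error term is of the right size.

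**The case against.** The strongest reply is that this is a condensed article. The wording of section 2.3 is compatible with allocation inside matched sets, and set, block and covariate details may stand in a fuller document. That much is fair: silence on how the sequence was built is not itself a fault. What remains is that the article does name the primary model, and that model omits a design feature the article also states.

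A second reply is that the Group × Time error term already excludes stable differences in strength. Age and activity would have to predict the course of recovery, in a sample narrowed to trained men aged 18–35. This stands, and it is why the loss is conditional and may be nil. A third is that modelling the sets costs a third of the error degrees of freedom. That is also true, but the price in power is at most about 0.01.

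Two stronger readings are tempting and not supported:

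- A reader might infer that the list ignores the matching and that the error term is therefore too large. These cannot both hold: if the list ignores the matching, the error term is correct.
- A reader might infer an unrestricted list that leaves the arms unequal. The article describes no such list, and section 2.4 gives 15 per group, which fits a fixed-size list at least as well.

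**Conclusion.** The mismatch holds on the text: matching is stated in section 2.3, and neither the described sequence nor the model in section 2.7 refers to it. Confidence in that is high.

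The statistical consequence is conditional. It requires allocation within sets and some relation between age or activity and change in strength. Under the assumed conditions it ranges from no loss, through about 0.05 of power at 10% of change explained (0.904 − 0.855), to about 0.11 at 20% (0.945 − 0.837). No documented figure places the trial within that range, so confidence in the size is moderate to low. Any error is towards a conservative test; it does not raise the false-positive rate or bias the estimate. Severity is minor to moderate.

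**What to change.** **Section 2.3.** Either state that the three arms are randomly permuted within each matched set of three (or in permuted blocks within age × IPAQ strata), and how the sets or strata are formed; or delete the matching sentence. The section places matching after recruitment, so permutation within sets appears feasible.

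**Section 2.7.** Add age and IPAQ MET-min/week, or the matched set, to the primary model together with their interactions with time. The interactions are essential: a covariate that is constant over time leaves the Group × Time test unchanged.

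**Cost.** A few sentences and no new data, since age and IPAQ are already collected. With 36 men, the two covariates take 10 of 165 error degrees of freedom and the matched sets take 55. If matching explains none of the change, the loss of power with matched sets is at most about 0.01.

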#### Participant blinding

2.3.1

All participants will use the same gas administration system (MITOVIT Hypoxic Training System, MITOVIT, Germany) with identical masks and external configurations, regardless of group allocation (IH, HH, or placebo). The device interface will remain concealed during the intervention, and perceptual differences between gas mixtures (FiO_2_ ≈ 12%, 21%, or 30%–35%) are minimal, thereby substantially reducing the likelihood that participants will consciously identify their experimental condition.

#### Evaluator blinding

2.3.2

Personnel responsible for data collection—including physical, cognitive, psychological, and biochemical assessments—will be blinded to participants’ group assignments. To avoid inadvertent unblinding (e.g., when a protocol involves cycling exercise), the staff operating and supervising the MITOVIT Hypoxic Training System will not overlap with those conducting outcome assessments.

#### Data analyst blinding

2.3.3

The dataset will be delivered to the statistician in coded format, using neutral identifiers (e.g., Group A, B, C). No information that could reveal the intervention type will be included. The correspondence between group codes and interventions will be known only to an external technician not involved in data collection or statistical analysis.

### Sample size

2.4

The primary outcome of this trial is hamstring isometric strength. The required sample size was determined *a priori* using G*Power 3.1 considering a repeated measures of variance (ANOVA) design. In the absence of prior data to inform the expected magnitude of change, a conventional medium effect size (*f* = 0.25), as defined by Cohen, was assumed. With a significance level of *α* = 0.05, a statistical power of 0.80 (*β* = 0.20), and six time points, the analysis indicated that 36 participants would be required to detect statistically significant differences between groups. To account for potential dropouts and non-compliance, an additional 20% contingency was applied, increasing the total sample size to 45 participants (15 per group).

### Interventions and protocol

2.5

The intervention process will last for five days (Figure 1), with breathing intervention administered from Day 1 following the DOMS induction protocol. All participants will be instructed to maintain their habitual training routines.

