**Figure 1 F1:**
[figure not shown]
Flow diagram showing the process of the intervention.

Additionally, participants will be asked to avoid physical activity for at least 48 h prior to the study, to ensure baseline resting metabolic state.

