#### Safety considerations

2.5.4

Peripheral oxygen saturation (SpO_2_) and heart rate will be continuously monitored. The system is equipped with two pulse oximeters and prevents SpO_2_ from dropping below the safety threshold of 80%. In addition to real-time SpO_2_ and heart rate monitoring, participants will be verbally screened before each session for symptoms such as dizziness, nausea, headache, excessive fatigue, or discomfort related to mask use (24).

Adverse events will be defined as any unfavorable or unintended signs, symptoms, or physiological responses occurring during or after the intervention sessions, whether or not they are considered related to hypoxic exposure (19). Criteria for immediate interruption of the session will include a sustained SpO_2_ below 80%, abnormal cardiovascular responses, onset of moderate-to-severe symptoms, or participant request to stop the session (24).

In the event of an adverse response, the hypoxic stimulus will be immediately terminated, normoxic breathing will be restored, and the participant will be placed in a seated or supine position as appropriate (24). All adverse events will be documented and reported, and participants experiencing significant adverse responses will be withdrawn from the study and referred for medical evaluation if necessary (19).

Participants will also be advised to drink water after each hypoxia session. Equipment will be disinfected after use with an ozone treatment box (Ozone Treatment and Disinfection Box, JBM, Spain) to eliminate bacteria, viruses, and fungi.

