#### Additional considerations

2.5.5

All participants will be instructed to refrain from engaging in any additional strenuous physical activity involving the lower limbs throughout the intervention period in order to avoid interference with the DOMS recovery process (4). Light daily activities and upper-limb training will be permitted, provided that they do not induce significant muscular fatigue or soreness (4).

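### Sections 2.5 and 2.5.5 give conflicting instructions on leg training during the five intervention days, which would add avoidable noise to the primary endpoint

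*Protocol article*

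**What the plan says.** Section 2.5 (Interventions and protocol) opens by saying that the intervention lasts five days, with breathing sessions from Day 1 after DOMS induction. Its next sentence reads: "All participants will be instructed to maintain their habitual training routines".

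Section 2.5.5 (Additional considerations) tells all participants to "refrain from engaging in any additional strenuous physical activity involving the lower limbs throughout the intervention period", and gives the purpose: "in order to avoid interference with the DOMS recovery process". It then adds: "Light daily activities and upper-limb training will be permitted", on condition that these cause no significant fatigue or soreness.

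Three other places bear on the point:

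- Under Figure 1, "participants will be asked to avoid physical activity for at least 48 h prior to the study". This covers only the time before the study.
- Section 2.2 recruits men who "engage in at least two organized training sessions per week", through university teams, sports clubs and training groups.
- Sections 2.4 and 2.6 make hamstring isometric strength the primary outcome, and Table 1 schedules it on Days 1 to 5.

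**The concern.** Both sentences are instructions to every participant, and both are attached to the same five days. For these participants, habitual training may well include running, jumping or lower-body resistance work. Keeping the routine then means loading the hamstrings while they recover, which 2.5.5 sets out to prevent.

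The primary endpoint, soreness and CK are all measured in that window. If some participants keep training their legs and others stop, recovery will vary for reasons unrelated to the gas mixture. A treatment effect becomes harder to see, and with 15 per arm the number who trained can easily differ between arms by chance.

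**Working it through.** **1. The texts side by side**

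| | Section 2.5 | Section 2.5.5 |
|---|---|---|
| Who | All participants | All participants |
| When | No period named; follows directly on the five-day description | The whole intervention period |
| Strenuous leg training | Continues, if habitual | Not to be done |
| Reason given | None | Protects DOMS recovery |

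Two readings might remove the conflict.

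- *The word "additional" in 2.5.5 means beyond habitual training.* The next sentence of 2.5.5 lists what is allowed: light daily activity and non-fatiguing upper-limb work. Habitual strenuous leg sessions fit neither.
- *The 2.5 sentence concerns the run-in.* It follows directly on the description of the five intervention days. The one stated pre-study rule, the 48 h rest, asks for the opposite of continued training.

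**2. The plan's own sample size**

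Section 2.4 gives 36 evaluable participants (f = 0.25, alpha 0.05, power 0.80, six time points), raised by a 20% allowance to 45. The allowance reproduces: 36 / (1 − 0.20) = 45. The 36 cannot be fully checked, because no correlation among repeated measures is stated. For the Group × Time test with three groups, six times and sphericity, a noncentral F calculation in G*Power's default form gives N = 36 (power 0.82) at a correlation of 0.25, and N = 24 (power 0.96 at 36) at a correlation of 0.5. The 36 is taken as given below.

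**3. Cost in participants (assumed inputs)**

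The article does not say how many participants would train legs or how far this would alter recovery. Let a share p do so between the Day 1 baseline and the Day 5 test, and let this shift their strength change by d residual SDs. The mixture adds variance p(1 − p)d², so

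variance factor = 1 + p(1 − p)d², and required N ≈ 36 × factor.

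| d | p = 0.25 or 0.75 | p = 0.5 |
|---|---|---|
| 0.25 | 1.012 → 36.4 | 1.016 → 36.6 |
| 0.5 | 1.047 → 37.7 | 1.063 → 38.3 |
| 1 | 1.188 → 42.8 | 1.250 → 45.0 |

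Rounded up, this is 37, then 38 to 39, then 43 to 45. At d = 1 and p = 0.5, the extra need of 9 equals the whole allowance (45 − 36 = 9).

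**4. Power in the worst case of the table**

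Dividing f² = 0.0625 by 1.25 at N = 36, interaction power falls from 0.82 to 0.71 at a correlation of 0.25, and from 0.96 to 0.90 at a correlation of 0.5.

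**5. Chance imbalance**

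Treat the number who trained in each arm as independent Binomial(15, p). Exact enumeration gives P(largest − smallest ≥ 4) = 0.296 at p = 0.25 or 0.75, and 0.406 at p = 0.5. This is part of the same noise as in step 3, not a further harm.

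**The case against.** The strongest reply is that the operative rule can be identified. Section 2.5.5 is explicit about who, when and why, and a careful reader would follow it. The 2.5 sentence names no period of its own, the text after it turns to conduct before the study, and Figure 1 is not available to settle the matter. The wording actually given to participants is not shown either, so mixed compliance is a supposition.

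The size is also hypothetical. For d up to 0.5 the cost is one to three participants. The costly case needs half the sample to train legs and a shift of a full SD. Section 2.4 says its allowance covers non-compliance as well as dropout, so part of this cost may already be budgeted. If the correlation is 0.5 rather than 0.25, power stays at 0.90 even in that case.

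Much of this stands as a limit on the size: the harm may be small, and it depends on inputs that the article does not give. It does not remove the conflict. A participant who trains legs because 2.5 said to keep training is following an instruction, and a non-compliance allowance is a poor remedy for a sentence that can simply be corrected. Nor is this a detail left to a fuller document, since the article states both instructions.

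**Conclusion.** The concern holds. Sections 2.5 and 2.5.5 conflict over strenuous leg training on Days 1 to 5, and no other text resolves it. Section 2.5.5 is very probably the intended rule.

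The consequence is mainly lost precision on the primary endpoint. It is negligible to small if leg training shifts recovery by half a residual SD or less, and material only if the shift is near a full SD in a sizeable share of participants. This rests on assumed p and d, and on taking the stated 36 as correct. Because all arms receive the same instruction under randomization and blinding, bias between arms is possible but not demonstrated. The point does not threaten the trial's validity, but it should be corrected before participants are instructed.

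**What to change.** - Keep 2.5.5 as the single rule.
- Delete the habitual-training sentence in 2.5. Alternatively, limit it to the time before the 48 h pre-study rest and, on Days 1 to 5, to upper-limb training.
- In 2.5.5, replace the wording on additional strenuous activity so that it covers any strenuous physical activity other than the study tests. The exception is needed because sprint, jump and squat tests run daily.
- Use the same wording in the participant materials.
- Section 2.5.4 already provides that "participants will be verbally screened before each session for symptoms such as dizziness". Add one question there on lower-limb training since the last visit, and report the answers descriptively by arm. Label any analysis that uses them exploratory, because the variable arises after randomization.

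The wording changes resolve the contradiction; the screening question is a useful addition that shows whether the rule was followed. The cost is one sentence deleted or limited, one phrase changed, and one question added to an existing daily check, with no extra visits or tests.
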